### The content of the sessions

HT for pregnant women with severe FOC in the present study comprises a combination of skills, taught in eight sessions of one hour between gestational week 16 and 36. Preferably, the partner of the pregnant woman also attends every session and participates actively in several exercises. If the partner, mostly the father, has the capacity for affirmative affective contact, in connection with his/her partner and their child, (s)he helps to create an atmosphere of safety, security and trust for the pregnant women. If the partner is not (yet) comfortable with this, the haptotherapist can guide him/her in this with some simple exercises. Similarly, the affective affirming contact between partners can be just self-evident. The content of the separate sessions will be briefly described below.

#### Session 1: Intake

Introduction, getting to know each other, taking an anamnesis, and making an agreement on the working methods of HT as defined in a treatment guideline. The first session is mainly an informative and administrative meeting.

#### Session 2: Ability to open and close

Introduction into the human ability to open and close to the awareness of sense impressions and the experience of its physical consequences. After this, the pregnant woman and her partner are taught to feel the difference between emotionally (affective) turning towards and turning away from another person. Once this is clear, this skill is applied in an exercise for the parents directed to the foetus by invitingly touching the woman’s belly. The foetus in the belly may respond by moving towards the touching hand. The confrontation with the ability to open up or to shut to the awareness of sensate impressions is the essence of the HT intervention which is the basis of the therapy.

#### Session 3: Further development of the ability to open and close

It is necessary to repeat the introductory exercises several times, because women with FOC, who are often blocked by their fear, may have difficulty to open up for sensate impressions. At the end of the session the exercise with invitingly touching the woman’s belly and the reactions of the baby may be further explored. The movements of the baby can help the pregnant woman to get familiar with the sensations of her body, because the movements of the baby from the inside draw the woman’s attention.

#### Session 4: Sensibilisation

HT stresses the importance of a sensitive interaction between the woman and her foetus and her (lower) body in order to facilitate the delivery proces. Whereas the first three sessions can be seen as a preparation, in the fourth session the attention will be directed to the belly and pelvic area of the pregnant woman. New exercises are performed to sensitize this part of the body. At the end of the session, the exercise in which the woman’s belly is touched and the reactions of the baby are further explored, which is meant to increase sensitivity of both parents gradually.

#### Session 5: Abdominal press

The aim of the fifth session is to practice the right use of abdominal pushing during childbirth. Therefore, all the aspects of opening for sensate impressions, interaction between the mother and her foetus, emotionally turning towards the childbirth process and emotional reactions in general will be paid attention to. At the end of the session, there again is a rehearsal of the belly touch exercise.

#### Session 6: Absorbing contractions and dealing with pain

The aim of this session is to practice coping with uterine contractions and dealing with pain during the delivery. Therefore all aspects dealt with in previous sessions, will again be paid attention to and at the end of this sixth session, as a recurrent theme, the focus again will be on invitingly touching the woman’s belly.

#### Session 7: Labour and delivery simulation

This seventh session consists of a training of labour by simulating all the aspects of labour as far as possible. Abdominal press and coping with contractions and dealing with pain in various positions are practiced. Attention is also paid to the role of the partner during labour and delivery.

#### Session 8: Evaluation and rehearsal

Evaluation of and, if necessary, rehearsal of exercises are the main components of this last session.

### Psycho education via internet condition

During gestation weeks 20–36, the Internet Group follows a course in eight modules via the Internet providing information about pregnancy and labour and delivery [47]. The entire process, from the beginning of the pregnancy to the delivery and post partum period is described. In this way, the pregnant woman can increase her knowledge about the normal course of pregnancy and delivery. Each week, the participant has the opportunity to ask questions about her own situation. The program covers a period of 8 weeks. In the first week, there is information about the development of the embryo and changes in the mother’s body in the first trimester. In the second week, the information addresses how these developments and processes continue during the second part of the pregnancy (the second trimester). The third week focuses on everything that happens in the final phase of the pregnancy (the third trimester). The fourth week begins with information on preparation for the delivery and important points to ponder in view of this major event. There is attention to what happens when labour begins. The fifth week is devoted to the options for pain management during labour and delivery, the various methods available and what the woman herself can do. In the sixth week, the course continues focussing on labour and delivery, in particular on what happens during the second and third phase of labour. In the seventh week possible emergencies that can occur during the delivery are discussed, what can happen and what is done in such case, including emergency caesarean sections. Week eight, the closing session, focus on the final part of the delivery: birth of the placenta (third stage of labour) and on the first days postpartum.

### Care as usual group

The Care as Usual Group receives care as usual according to the standards of the Royal Dutch Organisation of Midwives (Koninklijke Nederlandse Organisatie van Verloskundigen, KNOV) and the Dutch Organization of Obstetrics and Gynaecology (Nederlandse Vereniging voor Obstetrie en Gynaecologie, NVOG).

### Low FOC comparison group

The low FOC Comparison Group receives care as usual.

## Statistical analyses and power analysis

### Statistical analyses

To answer the primary research questions, we will use descriptive statistics (M and SD), between-subjects analysis of variance (ANOVA), followed by two planned pair wise comparisons (HT treatment versus care as usual, and HT treatment versus internetgroup).To maintain the experiment-wise Type I error rate at the 5% level, we use a Bonferroni corrected alpha of 0.05/2 = 0.025 for each single comparison. Clinical significance of the HT intervention will be tested both according to Jacobson and Truax’s criteria of reliable and clinical change [48] and by examination of the number of participants changing W-DEQ score from above to below a cut off score of 85. For the secondary research questions, we will use multiple regression, with `distress, depression, anxiety, somatization, PTSD symptoms, birth complications` as dependent variables, intervention (care as usual, psycho education via internet, and haptotherapy) as independent variable, and `background variables, social support, FOC` as covariates.

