### Randomisation

Randomisation is arranged by computer-generated numbers by means of the program RANDOM.ORG, that has provided a random list of thousand numbers 1, 2 and 3 [36]. An eligible pregnant woman with a W-DEQ A score ≥ 85 gets a number of 1, 2 or 3 in the order of the list. Those with the numbers 1, 2, and 3 are assigned to the HT Group, the Internet Group and Care as usual Group respectively.

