### Timing of measurement

All participants answer questionnaires by internet at the following four moments (see Figure 2):

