**Schematic representation of the design and procedure of this study.**

**T1:** admission to the study in weeks 20–24 of gestation. Measures: W-WDEQ A, 4DKL, HADS, SSQ, PRAM, demographic characteristics.**T2:** week 36 of gestation. Measures: W-WDEQ A, 4DKL, HADS, SSQ, PRAM.**T3:** 6 weeks postpartum. Measures: W-WDEQ B, PRAM, TES, Birth evaluation questionnaire.**T4:** 6 months postpartum. Measures: W-WDEQ A, 4DKL, HADS, SSQ, PRAM, TES.

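### The primary W-DEQ comparison is an ANOVA without baseline W-DEQ A: valid, but it gives up a modest amount of precision that costs nothing to recover

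*Protocol article*

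**What the plan says.** The Statistical analyses section fixes the primary model: "we will use descriptive statistics (M and SD), between-subjects analysis of variance (ANOVA), followed by two planned pair wise comparisons" (HT against care as usual, and HT against internet), each comparison tested at 0.025. It mentions no covariate, change score or time factor. Covariates appear in the next step only: "For the secondary research questions, we will use multiple regression", with background variables, social support and FOC as covariates.

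The baseline value exists for everyone. Under Randomisation, a woman receives an allocation number only if her W-DEQ A score is at least 85. Under Timing of measurement, "All participants answer questionnaires by internet at the following four moments"; T1 is "admission to the study in weeks 20–24 of gestation. Measures: W-WDEQ A, 4DKL, HADS, SSQ, PRAM, demographic characteristics" and T2 is "week 36 of gestation. Measures: W-WDEQ A, 4DKL, HADS, SSQ, PRAM".

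Allocation follows "a random list of thousand numbers 1, 2 and 3", used in order, and no blocking or stratification is described.

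Baseline fear does enter two supplementary analyses in the same section: reliable and clinical change, and the number of women who move from above to below 85.

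**The concern.** The strongest available predictor of fear at week 36 is probably fear at weeks 20–24 on the same scale. It is measured in every randomised woman and then left out of the comparison on which the trial will be judged. This has two consequences:

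- Outcome variance that baseline could explain stays in the error term, so confidence intervals are wider and power is lower than the data allow.
- With an unstratified list, the arms will differ somewhat in baseline fear by chance. The unadjusted estimate carries part of that difference.

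The sample size leaves little room. At best, the stated 64 per group gives almost exactly 80% power.

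**Working it through.** **Inputs from the article.** d = 0.5, alpha 0.025 per comparison, 80% power and 64 per group (Sample size calculation; sidedness not stated). FOC normally distributed and 6% severe (Background). Entry at W-DEQ A of 85 or more (Study participants; Randomisation).

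**Input not in the article.** The T1–T2 correlation ρ among all pregnant women. Assumed range 0.5 to 0.8.

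**Step 1: the plan's own figure.** Two-sample t test, noncentrality d·√(n/2) = 0.5·√32 = 2.83, 126 degrees of freedom.
- One-sided 0.025: 64 per group are needed, and power at 64 is 80.1%. This reproduces the stated figure, as does an uncorrected two-sided 0.05.
- Two-sided 0.025: 78 per group are needed, and power at 64 is 71.2%. This does not reproduce it.

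Both readings of 0.025 are carried forward.

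**Step 2: what selection does to the correlation.** The top 6% of a normal distribution lies above c = 1.555. The mean beyond c is λ = φ(c)/0.06 = 1.985. The baseline variance after selection, relative to the population, is v = 1 + cλ − λ² = 1 + 3.087 − 3.942 = 0.145, so the SD is 0.381 of the population SD. The within-trial correlation is

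r = ρ√v / √(ρ²v + 1 − ρ²).

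For ρ = 0.5: 0.190 / √(0.036 + 0.75) = 0.215. For ρ = 0.8: 0.305 / √(0.093 + 0.36) = 0.453.

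**Step 3: gain from adjustment.** The residual variance is multiplied by 1 − r², so the effective d is 0.5/√(1 − r²). Power at 64 per arm:

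| ρ (population) | r (trial) | Variance removed | Effective d | Power, two-sided 0.025 | Power, one-sided 0.025 |
|---|---|---|---|---|---|
| no adjustment | – | 0% | 0.500 | 71.2% | 80.1% |
| 0.5 | 0.215 | 4.6% | 0.512 | 73.4% | 82.0% |
| 0.6 | 0.275 | 7.5% | 0.520 | 74.9% | 83.1% |
| 0.7 | 0.350 | 12.2% | 0.534 | 77.3% | 85.0% |
| 0.8 | 0.453 | 20.5% | 0.561 | 81.6% | 88.3% |
| 0.87 (ceiling) | 0.558 | 31.1% | 0.602 | 87.1% | 92.2% |

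The last row is a ceiling. The 0.87 in the Fear of childbirth section is an internal-consistency and split-half reliability, which describes a single occasion. A correlation that high over 12 to 16 weeks would need true fear to be perfectly stable.

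**Step 4: chance imbalance.** With 64 per arm, the difference in mean baseline between two arms has standard error √(2/64) = 0.177 baseline SD (within the trial), a 95% range of about ±0.35 SD. The part carried into the unadjusted outcome difference is r times this: ±0.07 outcome SD at r = 0.215, ±0.12 at 0.350 and ±0.16 at 0.453, against a target effect of 0.5 SD.

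**The case against.** **The ANOVA is not wrong.** Randomisation makes the unadjusted comparison unbiased on average and keeps its type I error, and its standard error already allows for chance imbalance. This stands. A reader might infer that the primary test is biased or invalid; nothing in the article supports that.

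**The article does use baseline.** It does so in the reliable-change and cut-off analyses. This also stands, so the point is confined to the primary comparison. Those analyses do not adjust the planned contrasts.

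**The ANOVA might be run on change scores.** The section names neither the time point nor the form of the response, and a change score would use baseline. But nothing in the text points that way, and the first research question asks whether fear is lower after treatment.

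**This is a condensed article, and covariates may be settled elsewhere.** That would count if the article were silent. It states the primary model and says where covariates are used.

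**The gain is small.** This largely stands. For ρ of 0.5 to 0.7 it is about 2 to 6 points of power at two-sided 0.025, and power stays below 80%. A reader might infer that adjustment makes up a power shortfall. That does not follow: whether there is a shortfall depends on a sidedness that the article does not state, and this is a separate question.

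**Conclusion.** The point holds as one of efficiency. The primary comparison is stated without the baseline score, which is complete for all randomised women, and the unadjusted ANOVA, though valid, is less precise than it need be and leaves chance imbalance in the estimate.

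The likely size is modest: about 5% to 21% of residual variance, worth roughly 2 to 10 points of power at two-sided 0.025 (71% to 73–82%) or 2 to 8 points at one-sided 0.025 (80% to 82–88%). This rests on an assumed population correlation of 0.5 to 0.8 and on the article's own statements that FOC is normally distributed and 6% of women are severe. If the trial sample is less sharply truncated than these imply, the gain would be larger; a weaker correlation would make it smaller.

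**What to change.** Make the primary analysis an ANCOVA, or an equivalent linear mixed model, of post-intervention (T2) W-DEQ A on arm with T1 W-DEQ A as covariate. Take the two planned contrasts (HT versus care as usual, HT versus internet) from that model, each at 0.025 and with a confidence interval. The Statistical analyses section names no time point, so the same sentence should confirm that T2 is the primary one.

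The cost is one sentence, settled before outcome data are analysed so that no choice between adjusted and unadjusted results arises later. It needs no new data and no more participants. Present the change as a gain in precision and leave the sample size statement to be justified on its own terms.

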**Methods/Design:**

Included are singleton pregnant women with severe fear of childbirth, age ≥ 18 year, randomised into three arms: (1) treatment with haptotherapy, (2) internet psycho-education or (3) care as usual. The main study outcome is fear of childbirth. Measurements are taken at baseline in gestation week 20–24, directly after the intervention is completed in gestation week 36, six weeks postpartum and six months postpartum. Secondary study outcomes are distress, general anxiety, depression, somatization, social support, mother-child bonding, pregnancy and delivery complications, traumatic anxiety symptoms, duration of delivery, birth weight, and care satisfaction.

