
### Aims

The main goal of this study is to evaluate the effectiveness of HT in reducing severe FOC, in comparison to (1) psycho education about pregnancy and childbirth, and (2) to care as usual. We also study how effectiveness is related to background variables including perceived distress, social support, and complications in pregnancy.

The following research questions are addressed:Do FOC women with severe FOC after HT treatment have a lower FOC than women who receive psycho education about pregnancy and childbirth via the internet or who have care as usual?Do women with severe FOC after HT treatment (1) have a better emotional bonding with their child during pregnancy and postpartum and (2) have fewer complications requiring forceps, vacuum extraction, or cesarean delivery and less third degree tears or episiotomy, (3) have lower levels of distress, depression, anxiety, PTSD symptoms and somatization, than women who receive psycho education about pregnancy and childbirth via the internet or who have care as usual?

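### The stated 5% experiment-wise error covers two contrasts at one visit, but fear of childbirth has three follow-up measurements and none is named primary

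*Protocol article*

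**What the plan says.** The section on statistical analyses plans a "between-subjects analysis of variance (ANOVA") on the primary question, "followed by two planned pair wise comparisons (HT treatment versus care as usual, and HT treatment versus internetgroup"). On the error rate it says: "To maintain the experiment-wise Type I error rate at the 5% level", "we use a Bonferroni corrected alpha of 0.05/2 = 0.025 for each single comparison".

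The abstract says "The main study outcome is fear of childbirth" and attaches no visit to it. It lists the measurements after baseline as "directly after the intervention is completed in gestation week 36, six weeks postpartum and six months postpartum". The section on timing has participants answer questionnaires "at the following four moments" and gives the instrument for each: W-DEQ A at T1 (weeks 20–24), W-DEQ A at T2 (week 36), W-DEQ B at T3 (6 weeks postpartum) and W-DEQ A at T4 (6 months postpartum).

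The primary research question under Aims asks whether women "after HT treatment have a lower FOC than women who receive psycho education about pregnancy and childbirth via the internet" or who have usual care. It names no visit. The sample size section refers to the primary research question and names none either.

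**The concern.** The article makes an unconditional statement about the error rate of the whole experiment and shows the divisor behind it. The divisor is the number of contrasts. The number of occasions on which the main outcome is measured does not enter, and nothing in the described analysis reduces three occasions to one: the ANOVA is between subjects, so it compares arms at a given visit and does not pool visits.

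The three measurements are also not repeats of one quantity. T3 uses version B and the other two use version A, and the abbreviations list defines A as prepartum and B as postpartum fear. Fear before birth, fear recalled after birth and fear half a year later can answer differently to the same intervention. If the choice among them stays open until the data are seen, the false-positive guarantee on the main outcome is lost.

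**Working it through.** **Inputs from the article.** Overall alpha 0.05, two contrasts, 0.025 each (Statistical analyses); follow-ups T2, T3, T4 (Timing of measurement); d = 0.5 and 64 per arm (Sample size calculation).

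**Assumed, because the article does not give them.** Two-sided tests; the same correlation between any two visits, run from 0 to 0.9.

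**Step 1: the article's own figure.** 0.05/2 = 0.025, and the Bonferroni bound is 2 × 0.025 = 0.05. Two independent tests would give 1 − 0.975² = 0.0494. The two contrasts share the haptotherapy arm and are positively correlated; by simulation the chance of at least one false rejection is 4.6%, or 3.6% if the ANOVA must first be significant at 5%. At one visit the claim holds.

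**Step 2: three visits.** There are 2 × 3 = 6 tests. The bound is 6 × 0.025 = 0.15; six independent tests would give 1 − 0.975⁶ = 0.141. For the actual structure, 400,000 trials were simulated with no effect anywhere. Each contrast is the difference of two standardised arm means divided by √2, rejected if its absolute value exceeds the normal quantile for 1 − 0.025/2. An error is any rejection among the six.

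| Between-visit correlation | No ANOVA gate | ANOVA significant first, at each visit |
|---|---|---|
| 0 | 13.2% | 10.3% |
| 0.3 | 12.7% | 9.9% |
| 0.5 | 11.9% | 9.4% |
| 0.7 | 10.4% | 8.2% |
| 0.9 | 8.0% | 6.3% |
| One visit only | 4.6% | 3.6% |

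**Step 3: two ways to restore 5%.**
- Fix one visit: error returns to 4.6% with alpha unchanged.
- Correct for all six tests: 0.05/6 = 0.0083. With n = 2(z₁₋α/₂ + z₀.₈)²/d² = 2(2.638 + 0.842)²/0.25 ≈ 97 per arm (99 with the t distribution). At 64 per arm, power would be 56%.

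**Step 4: Holm against single-step Bonferroni at one visit.** Holm compares the smaller p-value with 0.025 and, if that passes, the other with 0.05. Setting: 64 per arm, pooled error with 3 × 64 − 3 = 189 degrees of freedom, non-centrality 0.5 × √(64/2) = 2.83, no ANOVA gate, d = 0.5 against both controls.

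| Power | Bonferroni | Holm |
|---|---|---|
| Each comparison | 71.5% | 76.8% |
| Both comparisons | 57.6% | 68.1% |
| At least one | 85.4% | 85.4% |

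If the effect against the second control is only d = 0.25, the d = 0.5 contrast goes from 71.5% to 72.2% and the weaker one from 20.1% to 27.7%.

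These power figures depend on two-sided testing. The article does not state sidedness and claims at least 80%. With 64 per arm and d = 0.5, a two-sample t-test has 80.1% power at one-sided 0.025 but 71.2% at two-sided 0.025. That mismatch is a separate question.

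**The case against.** The best defence is that the article leans towards week 36. The primary question speaks of fear after treatment, the abstract places week 36 directly after the intervention, and T2 is the only follow-up at which version A is completed before the birth. A condensed article may also leave the designation of a primary visit to an analysis plan. This is fair as to the likely intention. It does not make the published sentence true as it stands: the article lists three follow-ups without ranking them and still states 5% for the experiment.

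Three stronger readings are tempting, and the documents do not support them.

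- *That success may be claimed on the best of six tests.* The article describes one ANOVA and two planned comparisons. It sets no any-visit rule. It fails to exclude one, which is less.
- *That 8 to 13% is the chance of a false claim for haptotherapy.* The figure counts errors in both directions. Counting only false superiority of haptotherapy under two-sided tests gives about 6.4, 6.0, 5.2 and 4% at correlations 0.3, 0.5, 0.7 and 0.9, or about 5.0, 4.7, 4.1 and 3% behind the ANOVA, against 2.3% at one visit without the gate. The inflation is still roughly two- to threefold without the gate, but the level is lower.
- *That Bonferroni after an ANOVA is a mistake.* It is valid for two planned contrasts, only conservative. The article does not require haptotherapy to beat both controls, so the power for both comparisons answers a success rule that it does not set. Holm also does nothing for the three visits.

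**Conclusion.** The point holds in a limited form. The correction is right for two contrasts at one visit, and the experiment-wise claim depends on a choice of visit that the article never makes. How far error could rise is conditional on all three visits being tested, on any significant result counting and on correlations that are not in the article. Every correlation run from 0 to 0.9 gives a two-sided rate above 5%, with or without the ANOVA gate; only as the correlation approaches 1 does it return to the one-visit value. This should be corrected because it concerns the false-positive guarantee on the main outcome and the correction needs no additional participants. The Holm gain of about 5 percentage points per comparison is a recommendation only; it assumes two-sided tests and equal effects of d = 0.5, and it shrinks to under 1 point for the stronger contrast when the other effect is d = 0.25.

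**What to change.** State one fear-of-childbirth measurement, with its visit and W-DEQ version, as the primary endpoint. W-DEQ A at week 36 is the natural choice. Analyse it with the baseline W-DEQ A score, already collected at T1, as a covariate. Declare the 6-week and 6-month measurements secondary, outside the 5% claim. The level of 0.025 per contrast then delivers what the article says.

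Optionally, test the two contrasts directly, without the ANOVA as a precondition, using Holm: the smaller p-value against 0.025, then the other against 0.05. This keeps the same error rate.

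The cost is about two sentences and no change to recruitment. The postpartum results lose confirmatory standing, which matters if the investigators regard lasting fear reduction as the main claim; in that case they should name that visit instead, before seeing data by arm. Under Holm, matching confidence intervals are less simple; reporting 97.5% intervals for both contrasts is a workable, slightly conservative substitute.

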### Measures

#### Background variables

General issues concerning the birth and background factors will be assessed using a questionnaire which has been especially designed for this study to collect information about demographic characteristics and the participants’ perception on health care in connection to pregnancy and delivery.

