#### Distress, anxiety, depression, somatization

Distress, Anxiety, Depression and Somatization will all be measured with the `Four Dimensional Symptom Questionnaire` (4DSQ) [38]. The 4DSQ consists of a list of 50 symptoms of psychological and psychosomatic symptoms according to DSM IV [4].The 4DSQ measures distress, depression, general anxiety and somatization as separate dimensions. The 4DSQ scales have a high internal consistency (Cronbach’s alpha: 0.84 to 0.94) [39, 40].

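### The covariate list for the secondary regressions does not name the outcome's own T1 score, although the 4DSQ and HADS are collected at T1, so precision is given up on depression, anxiety and somatization

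*Protocol article*

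**What the plan says.** The Statistical analyses section sets one model family for the secondary questions: "we will use multiple regression, with `distress, depression, anxiety, somatization, PTSD symptoms, birth complications` as dependent variables". The rest of the same sentence gives the predictors: "intervention (care as usual, psycho education via internet, and haptotherapy) as independent variable, and `background variables, social support, FOC` as covariates".

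Two places describe what background variables are. Under Measures, a purpose-built questionnaire is to "collect information about demographic characteristics and the participants’ perception on health care in connection to pregnancy and delivery". The Aims speak of "background variables including perceived distress, social support, and complications in pregnancy".

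The schedule under Timing of measurement says "All participants answer questionnaires by internet at the following four moments". T1 is "admission to the study in weeks 20–24 of gestation. Measures: W-WDEQ A, 4DKL, HADS, SSQ, PRAM, demographic characteristics". The 4DKL and HADS appear again at T2 and T4. On the instrument, the Measures section says "The 4DSQ measures distress, depression, general anxiety and somatization as separate dimensions".

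**The concern.** When the same symptom scale is taken before and after treatment, the earlier score is usually among the best available predictors of the later one. Here the plan lists other covariates but not that score. Nowhere does the article provide a change-score, ANCOVA or repeated-measures model for these outcomes that would bring it in another way.

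At stake is the part of the second research question on distress, depression, anxiety and somatization. Its arm comparisons may have wider intervals than the collected data allow. Allocation follows a plain random list of 1, 2 and 3 with no stratification described, so a chance T1 difference in, say, HADS depression would pass partly into the T2 and T4 contrasts. Social support and FOC would absorb only some of it.

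**Working it through.** **1. Is a T1 score available?** The schedule puts the HADS at T1, which covers anxiety and depression. It also puts the 4DKL there. Read as the 4DSQ, this adds distress and somatization and gives a second measure of anxiety and depression. Somatization rests on that reading. The TES first appears at T3, and birth complications have no T1 value, so neither of those models is affected. I take the T1 scores as recorded before allocation. The schedule places them at admission, alongside the W-DEQ A that decides eligibility, but does not say so scale by scale.

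**2. Does the listed set already contain it?** The Measures description covers demographics and views of care. The Aims description adds perceived distress, social support and pregnancy complications. Distress can therefore be read as included. Depression, anxiety and somatization are named in neither place.

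**3. The plan's own figure.** The sample size section addresses only the primary question: d = 0.5, 80% power, alpha 0.025, 64 per group. With a two-sample t-test (126 df) and 64 per arm, power is 80.1% at two-sided 0.05 (one-sided 0.025 has the same critical value) and 71.2% at two-sided 0.025. There is no stated figure to reproduce for the secondary regressions, so what follows borrows d = 0.5 and 64 per arm for illustration only.

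**4. Chance imbalance.** The SD of the T1 mean difference between two arms of 64, in outcome SDs, is √(2/64) = 0.177. The 95% range is ±1.96 × 0.177 = ±0.35, and the probability of exceeding 0.25 is 15.7%. Let ρ be the T1-to-follow-up correlation. With no covariates, about ρ times the difference carries over. For a 0.35 SD imbalance that is 0.10, 0.17 or 0.24 SD at ρ = 0.3, 0.5 or 0.7. The listed covariates would reduce this.

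**5. Gain over the listed covariates.** The fair comparison is with the planned model, not with no adjustment. Assume that the listed covariates are pre-allocation, correlate c = 0.5 with the T1 score and relate to the outcome only through it. Then:

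- residual variance as planned = 1 − (ρc)²
- residual variance with the T1 score added = 1 − ρ²
- effective d = 0.5/√(residual variance), with power from the noncentral t at 64 per arm, two-sided 0.05, ignoring the few degrees of freedom spent on covariates.

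At ρ = 0.5, for example, the variances are 1 − 0.0625 = 0.9375 and 1 − 0.25 = 0.75. The effective d values are 0.516 and 0.577, and power is 82.6% and 90.0%.

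| ρ | Variance as planned | Variance with T1 | Ratio | Power as planned | Power with T1 | Gain (points) |
|---|---|---|---|---|---|---|
| 0.3 | 0.978 | 0.910 | 0.93 | 81.0% | 83.7% | 2.7 |
| 0.4 | 0.960 | 0.840 | 0.88 | 81.7% | 86.5% | 4.8 |
| 0.5 | 0.938 | 0.750 | 0.80 | 82.6% | 90.0% | 7.4 |
| 0.7 | 0.878 | 0.510 | 0.58 | 85.0% | 97.6% | 12.6 |

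The gain reaches 5 points at ρ a little above 0.4. If the listed covariates overlap more with the T1 score (c = 0.7), the gain is 1.8, 3.2 and 5.0 points at ρ = 0.3, 0.4 and 0.5. At two-sided 0.025 with c = 0.5 it is 3.3, 6.1 and 9.7 points.

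**The case against.** The strongest reply is that the text does not exclude the T1 score. The Aims introduce their list of background variables with *including*, so it is not exhaustive, and its first item, distress, is itself a 4DSQ dimension. The sentence in the analysis section is also condensed: it covers six outcomes by category label, with no time points and no choice between 4DSQ and HADS. A fuller analysis plan could contain the baseline term.

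Part of this stands. A reader might infer that, even on the widest reading, distress is the only T1 symptom score that could enter. The open wording of the Aims does not support that. What remains is that the article does print a covariate list, and on its natural reading three of the repeated symptom outcomes lack their own T1 score.

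The reply is also right about size. Setting 80.1% with no covariates against 90.0% with T1 adjustment at ρ = 0.5 would credit the T1 score with what the listed covariates already achieve. The d and alpha belong to the primary question, ρ is unknown, and T4 lies six months beyond delivery, so a high T1-to-T4 correlation cannot be presumed.

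A reader might further infer that, because entry is cut at a W-DEQ score of 85 and not on these scales, their T1 spread, and so the gain, is fuller than for the W-DEQ. The article gives no distribution for any of them, so this has no support.

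**Conclusion.** The point holds as a loss of efficiency on secondary outcomes. It is not a bias: with randomised arms and pre-allocation covariates, the planned contrast is right on average, and its standard error already reflects chance imbalance. Adding the T1 score would narrow that error and correct the imbalance that actually occurs.

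Under the stated assumptions the gain is small at ρ = 0.3 (2.7 points of power), moderate at 0.5 (7.4) and large at 0.7 (12.6). It rests on an assumed ρ, an assumed overlap of 0.5, borrowed design values, 64 analysed per arm and the reading of 4DKL as 4DSQ. The case is clearest for depression, anxiety and somatization. For distress it is a matter of making explicit what may already be meant.

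**What to change.** In the Statistical analyses section, state that each secondary regression whose outcome is measured at T1 includes the T1 score of that outcome, on the same instrument and subscale, as a covariate. This applies to 4DSQ distress, depression, anxiety and somatization, and to HADS anxiety and depression. Leave the models for PTSD symptoms (TES) and birth complications as they are. If background variables were already meant to cover these scores, the same sentence settles it.

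The cost is one sentence and one degree of freedom per model, with no new data. It should be made before the outcome data are analysed.
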